### Description of the *i-*PUSH program

*i*-PUSH is a comprehensive intervention that ultimately aims to improve the utilization of Reproductive and Maternal and Child Health (RMNCH) services among WRA and their young children in Kakamega and Nairobi Counties, by increasing knowledge about and (financial) access to RMNCH services as well as improving the quality of care of RMNCH services. In the original *i*-PUSH program that is the focus of this evaluation, households receive the first year of health insurance premium for free, while they are stimulated and supported to save for a 50% co-payment in the second year, and a 100% premium payment thereafter. The free provision in year one is expected to show the benefits of insurance to the selected households. The support for savings during the first year for a 50% co-payment in the second year is expected to install a habit of savings.^1^

The *i*-PUSH program utilizes innovative digital tools developed by both partners to enhance access to affordable and quality health care to low-income WRA and their families. Through *i*-PUSH, selected clinics participate in the “SafeCare” quality improvement program. Women receive the National Health Insurance Fund (NHIF) *SupaCover* at subsidized premiums on their mobile phone, using PAF’s so-called “health wallet.” The “health wallet” runs on the digital platform M-TIBA, which registers health care utilization at participating clinics, connecting patients, providers, and payers on one platform. PAF is piloting several other tools on this platform in addition to the health wallet, such as Connected Diagnostics for Malaria in Kisumu County, the MomCare program for antenatal and postnatal care in Kisumu and Nairobi Counties, and socio-economic mapping for UHC support in Kisumu County. CHVs are the first point-of-contact for women in the program. They make use of AMREF’s *Mjali* (Mobile Jamii Afya Link) tool for digital registration of household information and the mobile phone-based LEAP tool for training. The LEAP tool employs a mobile learning approach to train and empower CHVs using their mobile devices operating from any phone [9]. This enables the CHVs to learn at their own pace, and with their own mobile devices while in the community, providing both interpersonal and community aspects of learning. This evaluation study will focus on two of these spheres of interest supported by mobile tools: knowledge on health and health behavior and (financial) access to healthcare services; the quality upgrades at the health facilities cannot be evaluated with our study design because all *i*-PUSH clinics in our study area were already upgraded at baseline. A rough sketch to the implementation of enrolment, intervention, and assessment of the program is indicated in Table 1. The implementation of *i-*PUSH will not alter access to the usual health care services (including use of any medication) throughout the implementation of the program.

**Table 1 Tab1:**
[figure not shown]
Schedule of enrolment, interventions, and assessments

### The LEAP training tool for CHVs

Working with CHVs, *i*-PUSH will increase the knowledge on both RMNCH and on insurance/health financing among women and men in the treatment communities. To this end, CHVs receive additional training through the specially developed LEAP training tool (module) carried out by AMREF. This tool contains modules on specific health terrains of interest (notably, health promotion activities for children under 5, family planning, antenatal care (ANC), danger signs in pregnancy and after delivery, danger signs in children under 5, maternal and child health and nutrition, water safety, hygiene and sanitation) as well as on health savings and health insurance. The CHVs can follow this training on the smartphone that they will receive as part of their inclusion in the program. It complements the standard monthly training sessions of CHVs by AMREF.

AMREF can currently assess whether LEAP improves the knowledge of its CHVs because at the end of each training module, CHVs can participate in a quiz on the tool that tests their newly gained knowledge. We will examine whether the LEAP training tool on top of the standard training activities of CHVs translate into improving women and men’s knowledge and behavior on pre-specified topics. We will also assess whether CHVs’ time spent on LEAP, number of training modules completed, and scores on the LEAP quizzes predict impact on women and men in the communities.

### Subsidized access to NHIF SupaCover health insurance through the M-TIBA health wallet

The improved knowledge on health and health financing of women and men is also expected to translate into improved attitudes towards insurance and saving for health and insurance. To support these changes in knowledge and attitudes, WRA would receive the first year of their NHIF insurance premium at 100% subsidy and the second year at a 50% subsidy. The subsidies are expected to enhance initial enrolment in NHIF such that enrollees can experience first-hand the benefits of insurance. Moreover, this will allow women to be acquainted with regular savings for the insurance premium for the next year, such that they will get into the habit of recurrent savings and increasingly be able to frequently set aside small amounts of money.

An integral component of the *i*-PUSH program is the so-called “health wallet” on M-TIBA (a mobile payment platform). Most WRA in the target population have limited access to formal financial services such as bank savings accounts. The widespread availability of M-PESA opens a new avenue of change in this respect. To alleviate this constraint, *i*-PUSH offers women the opportunity to set aside money in a commitment savings device on their mobile phone. The only requirement is that the mobile number is registered on their personal name. This will allow them (and other people such as spouses, relatives) to transfer funds into the wallet through M-PESA, which are subsequently “reserved” for direct payment of medical costs at M-TIBA-connected health providers or for future payment of the annual insurance co-premium. This feature of the health wallet is expected to support women in their financial planning—funds transferred into the wallet are kept safe and secure until they are needed for health-related purposes. Additional small-scale interventions are added to the program to enhance further savings, such as the provision of a savings calendar. Thus, this component of the program expects to increase savings for health as well as uptake and renewal of health insurance among the target population.

Enrolment in health insurance is further facilitated through an additional feature of *i*-PUSH—CHVs can digitally enroll WRA and their household members (spouses, children, and other dependents) on the NHIF *SupaCover* as long as they have an ID or birth certificate available at the time of the CHV visit. The CHV uploads the required documents and takes care of the registration process on his or her smartphone (as provided by the *i*-PUSH program), saving the women from a lot of hassle in traveling back and forth to the insurance offices to hand over all the required documents and go through the administrative steps. In other words, *i*-PUSH is also expected to relieve logistical and time constraints to the uptake of insurance. Such a scheme enhances enrolment into insurance [9].

## Expected outcomes

Overall, the outcomes of interest for this evaluation study that are measured during the 18 months of follow-up include the following:

### Primary outcomes (health care utilization and health expenditures)

Absolute number of visits to any formal health care provider for treatment of illness or injury (to measure curative healthcare utilization), over the full period between baseline and endline.

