### Sample size

Sample size calculation followed Hemming et al. [7]’s study by fixing the number of clusters per arm to be 12 clusters, and then estimated the cluster size and total sample size. In the current study, it was assumed that the *i*-PUSH program could yield an effect size of 0.4 standard deviation in terms of health care utilization with an intracluster correlation (ICC) of *ρ* = 0.014. The estimates of the ICC were derived from Geng et al. [8]’s, study conducted in Nandi County which used high-frequency data on diaries on health-seeking behaviors and financial expenditures over 1 year (October 2012–October 2013). The calculation of the ICC was based on health care utilization measured as visits to any formal health provider, unconditional on reported health symptoms. It hypothesized a confidence interval of 95%, a margin-of-error of 5%, and a power of 80%. With a cluster size per arm of 12 clusters, and a total number of women per cluster of 10, the total sample size was 120 households per arm and 240 households for the full study.

To keep sample size at par, households that dropped out of the study before the start of the intervention were replaced with new eligible households on a rolling basis for a maximum period of six months, or until the program started.

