### Baseline and endline survey instruments

The quantitative evaluation starts with a baseline survey before the rollout of the *i*-PUSH program and is completed by an endline survey conducted approximately 1 year after the *i*-PUSH introduction. Both surveys include modules on household demographics, socio-economic indicators, food and non-food consumption indicators, financial inclusion, participation in community networks, as well as self-assessed health status, health-related knowledge and behavior, health care utilization and health expenditures, maternal health, mental health, intra-household decision-making processes, and gender dynamics. In addition, the endline survey will include a satisfaction module on participation in the *i*-PUSH program for women in the treatment areas only and will be collected virtually using telephone interviews due to the COVID-19 pandemic. The household head or the most knowledgeable household member responds to the household roster, household-level modules including health care utilization and expenditures, and questions about under-aged household members. The focal person for the modules on maternal health, intra-household decision-making and health knowledge and behavior is the WRA in the household. All remaining individual-level modules (mental health, preferred clinic, mobile money use, savings groups and financial instruments) are reported by all adult individuals in the household (Table 2 in Appendix).

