### Financial and health diaries

This study uses weekly financial and health diaries data collection methodology as its core research instrument, because this technique is well suited to address the research objectives by providing a granular insight into the financial lives and health-related decisions of participating households. The diaries are collected over the full study period between baseline and endline survey. The financial diaries record all financial transactions such as purchases, gifts, remittances, and loans, including those between household members in the 7 days prior to each interview. Transactions are described by type, incoming or outgoing cash, amount, purpose, transaction partner, and date. The health diaries provide a detailed picture of the incidence of illnesses and injuries, as well as preventive and curative health-seeking behavior. Health diaries collect data on all health events that occurred to any of the household members (respondents, their children and other household members) in the 7 days prior to each interview. This includes symptoms, whether any health care was sought, which health provider was visited, health services received, out-of-pocket health expenditures, date of onset of the symptoms, and date of provider visit(s).

Respondents to the weekly diaries interviews are all adults in the study households who are economically active (i.e., who handle money, excluding young adults who are still studying) and capable of conducting the interview (i.e., excluding very old-age or disabled household members). Emancipated minors, i.e., teenage girls who are a mother or who are pregnant, are also included as diaries respondent. The financial diaries are reported by each individual him- or herself. The health diaries can be reported by one individual for the entire household.

Data are collected through structured and formatted digital tools that allow to analyze data as they are recorded and improve data collection tools mid-course of the process. The short recall period drastically reduces recall bias and ensures that both major and minor illness episodes, including those with foregone care are reported. Because interviewers visit households weekly, they build a relationship of trust, which enables the diaries to capture also more sensitive health events. This is of particular importance in relation to capturing maternal and child health experiences.

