with *Y*_*ij*_, *X*_*ij*0_ the posttest and pretest/baseline measures of the outcome for the *ith* respondent from the jth cluster, respectively. Treament_*ij*_ is a dummy for being assigned to the treatment group. It takes one if the respondent belongs to the intervention cluster and zero if control. *α*_2_ is the ITT effect or the impact of the *i*-PUSH program. We will use an OLS model with standard errors clustered at the level of the community units.

In addition to pretest measures, all other baseline covariates such as age, education, socioeconomic status (wealth quintile), crowding (persons per room), and occupation, will also be included in Equation (1). Thus, in Equation (1), the treatment effect of the *i*-PSUH program *α*_2_ assesses the treatment difference on post-treatment outcome adjusted for baseline.

We will assess whether the *i*-PUSH will significantly contribute in empowering women. For self-reported surveys on women empowerment, we will construct a total score of women’s empowerment which is based on a factor analysis of the various domains on which the woman indicates that she has sole, joint, or no decision-making power within the household (for each domain, the decision-making binary indicator will be equal to 1 if the woman respondent makes the decision alone or jointly with her partner and 0 otherwise). This total score will be used as the dependent variable, and Equation (1) will be used to estimate the impact of *i*-PUSH program on women’s empowerment. Furthermore, we will follow Almås et al. (2018) to construct an alternative measure of women’s empowerment based on the decision in the empowerment game. This dependent variable will be the willingness-to-pay which is the share that the woman is willing to pay in order to receive the amount herself in private rather than giving a (higher) amount to her husband. Interim data analyses (e.g., for policy briefs) are done using baseline and weekly diaries data to inform the context and implementation of the research or *i*-PUSH program.

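### The primary outcome is an absolute visit count with no term for time observed, so a between-arm difference in diary completion after roll-out would bias the treatment contrast

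*Protocol article*

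**What the plan says.** All references are to the protocol article.

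- **Outcome.** Under Primary outcomes, the single primary measure is the "Absolute number of visits to any formal health care provider for treatment of illness or injury", taken "over the full period between baseline and endline". No per-week or per-person denominator is given, and the unit (individual or household) is not stated.
- **Window.** Expected outcomes describes outcomes "measured during the 18 months of follow-up". Baseline and endline survey instruments describes an "endline survey conducted approximately 1 year after the *i*-PUSH introduction". Together these put about 6 of the 18 months before roll-out.
- **Replacement.** Under Sample size, households that left before the intervention began were "replaced with new eligible households on a rolling basis for a maximum period of six months, or until the program started". No replacement is described for households that leave later.
- **Diaries.** Under Financial and health diaries, each interview covers events "in the 7 days prior to each interview", and no catch-up after a missed week is described. On people covered: "Health diaries collect data on all health events that occurred to any of the household members".
- **Analysis.** Data management and analysis specifies intention to treat with all randomised respondents, and an OLS ANCOVA in Equation (1). Its covariates are described as "In addition to pretest measures, all other baseline covariates such as age, education, socioeconomic status (wealth quintile), crowding (persons per room), and occupation". Neither weeks observed nor household size is named. The same section also mentions a pooled panel and a generalised linear mixed model for repeated measures, without a time unit, link or exposure term.

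**The concern.** A total over a fixed window compares like with like only if everyone is observed for the same share of that window. This design makes that unlikely: it has weekly interviews with a 7-day recall over about 18 months, rolling entry before roll-out, and apparently no replacement afterwards. A household that misses a quarter of its interviews will have a total about a quarter lower at the same rate of care-seeking.

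Under-observation that is equal in the two arms costs power. Unequal under-observation after roll-out does more harm, because randomisation does not protect against it. Treatment villages receive subsidised insurance, the health wallet and support from a trained volunteer during follow-up. Control villages wait until after endline. Households in both arms are asked for the same weekly interviews. Willingness to continue could therefore differ, in either direction, and the difference would appear in the primary result as more or fewer visits.

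**Working it through.** **1. The plan's own figure.** Inputs from Sample size: effect 0.4 SD, ICC 0.014, 12 clusters per arm, 5% significance level (taken as two-sided), 80% power.

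- Individually randomised n per arm = 2 × ((1.96 + 0.842)/0.4)² = 98.1.
- Cluster size with 12 clusters fixed: m = 98.1 × (1 − 0.014) / (12 − 98.1 × 0.014) = 9.1, rounded up to 10.
- 12 × 10 = 120 per arm, 240 in total. This agrees with the article.
- Design effect = 1 + 9 × 0.014 = 1.126. Normal-approximation power at 120 per arm is 0.83.

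The sample size is not in dispute.

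**2. Bias if completion differs by arm and the programme has no effect.** Let an arm complete a share c of the diary weeks in the window, at a constant visit rate, and let μ and SD describe the fully observed count. The expected recorded total is c × μ, so

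bias in SD units = (difference in c) × (μ/SD).

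The article gives neither quantity. Assume a gap of 0.05 to 0.10 and μ/SD of 0.5 to 2. The standard error of the contrast is √(2 × 1.126/120) = 0.137 SD. The type I error is P(|Z + bias/0.137| > 1.96).

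| Gap in completed weeks | μ/SD | Bias (SD) | Type I error |
|---|---|---|---|
| 0 | any | 0 | 5% |
| 5 points | 0.5 | 0.025 | 5.4% |
| 5 points | 2 | 0.10 | 11% |
| 10 points | 0.5 | 0.05 | 6.5% |
| 10 points | 1 | 0.10 | 11% |
| 10 points | 2 | 0.20 | 31% |

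The gap is a share of the whole window. If it arises only in the roughly 12 of 18 months after roll-out, a 10-point gap overall means a gap of 0.10 × 18/12 = 15 points in those months.

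On the ratio scale, completion of 95% against 85% gives 0.95/0.85 = 1.12 with no true effect.

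**3. Late entry.** A household that joins at month 6 of 18 is seen for 12/18 = 67% of the window, so its expected total is 33% low. Replacement ends by the time the programme starts, so the lost time is before roll-out.

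**4. Cost when coverage is equally incomplete in both arms.** Assume that 10% to 30% of households are seen for 50% to 67% of the window and that SD/μ is 0.6 to 1.0. Scale the full count to mean 1 and SD v, and let e be the share observed. The effective effect size is then

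d = 0.4 × v × E(e) / √(E(e²) × (v² + 1) − E(e)²).

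- Mildest case (10% of households at 67%, v = 1.0): E(e) = 0.967, E(e²) = 0.944, d = 0.396, power 0.82.
- Worst case (30% at 50%, v = 0.6): E(e) = 0.85, E(e²) = 0.775, d = 0.354, power 0.73.

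Power therefore falls from 0.83 to between about 0.73 and 0.82.

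**The case against.** Several counter-arguments have force.

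- **Zero scoring is not stated.** A reader might infer that the plan counts missed weeks as no visits. Nowhere does it say so. The pooled panel and the repeated-measures mixed model could leave a missed week out, and the error term of Equation (1) carries a time index. This stands as a limit on the claim. But a model of weekly rows would not estimate the full-period total that the outcome section defines, so the two still need to be reconciled.
- **A missed week might be recovered.** The diaries record visit dates, and data completeness is checked and followed up. Recovery is possible, but no catch-up recall is described.
- **Late entry.** A reader might take it as a source of bias. It precedes roll-out and cannot result from receiving the programme, so it mainly adds noise.
- **Household size.** A reader might conclude that larger households distort the contrast. Randomisation balances size in expectation, the baseline value absorbs part of it, and the covariate list is open-ended and already names crowding. If the unit is the individual, larger households do not automatically have larger counts. This is a matter of precision.
- **Completion may not differ.** Control villages receive the programme after endline, and the paid behavioural games are not restricted by arm. Nothing in the article shows unequal completion.
- **Details belong in an analysis plan.** Offsets and missed-interview rules often do. The point here is narrower: the article affirmatively fixes an absolute total and pairs it with a model that has no exposure term.

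**Conclusion.** The point holds in a conditional form. As written, the outcome and Equation (1) give partly observed households short totals. A between-arm difference in interview completion after roll-out would pass straight into the treatment estimate. For a gap of 5 to 10 points the bias is about 0.025 to 0.20 SD, at most half the 0.4 SD target.

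That range rests on assumed values for both the gap and the mean-to-SD ratio, on a constant visit rate, and on missed weeks not being recovered. The 31% type I error combines the upper end of both assumptions and is not a prediction. With equal completion this bias is zero and only the power loss remains. The documents do not support saying that the trial will be biased. They do support saying that the primary analysis is needlessly exposed to a bias that data already being collected could largely remove.

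**What to change.** 1. Analyse visits relative to observed time. Use a count mixed model with village clustering and log(completed diary weeks) as the offset, or log(person-weeks) if the unit is the household. An equivalent rate in Equation (1) would also serve.
2. State the unit of analysis.
3. State that a missed diary week is unobserved, not a week without visits.
4. If the unit is the household, add baseline household size as a covariate for precision.
5. Report completed diary weeks by arm.
6. Add a sensitivity analysis for informative dropout. The offset assumes that missed weeks resemble observed ones, which dropout related to health or care-seeking would violate.

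The counting window need not change for this purpose.

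**Cost.** No new data collection should be needed, since the household roster and the weekly interviews should supply the denominator. The result would be reported as a rate rather than a total, which is a little less direct and changes how the primary outcome is expressed. As the trial is under way, the change should be recorded as an amendment before outcomes are compared by arm.

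### The primary visit count starts at baseline rather than at roll-out, so it includes time when i-PUSH could have no effect; the power cost depends on a lead-in and an effect-size window that the protocol does not state

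*Protocol article*

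**What the plan says.** All references are to the protocol article.

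- **Primary outcomes:** an absolute number of visits to formal providers for illness or injury, counted "over the full period between baseline and endline".
- **Expected outcomes:** outcomes are "measured during the 18 months of follow-up".
- **Baseline and endline survey instruments:** the baseline survey precedes roll-out, and the evaluation is "completed by an endline survey conducted approximately 1 year after the *i*-PUSH introduction".
- **Sample size:** households that drop out before the intervention starts are replaced "on a rolling basis for a maximum period of six months, or until the program started". The assumed effect is 0.4 SD in health care utilization, with no time window attached.
- **Financial and health diaries:** "The diaries are collected over the full study period between baseline and endline survey". The diaries record the dates of provider visits. The Abstract, however, describes the diaries as lasting one year.
- **Study design and randomization procedure:** villages are paired on baseline data and then allocated by coin flip. Volunteers in treatment villages are trained on LEAP and only afterwards introduce the wallet and the insurance.
- **Data management and analysis:** Equation (1) regresses the posttest measure on the pretest measure and a treatment dummy. The text describes the resulting effect as a difference in an outcome measured after treatment.

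**The concern.** A visit made before roll-out cannot respond to i-PUSH. Summing such visits into the primary count leaves the expected difference between arms, in visits, unchanged. It increases the variance of the count, so the standardised effect shrinks and the trial becomes less able to detect the effect it was planned for.

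Two further difficulties follow from the same definition. First, the count is absolute and runs from baseline, yet households may enter as replacements after baseline, up to programme start. Those households cannot have a count over the full period. Second, the pre-roll-out diaries are measured with the same instrument as the outcome and would be a natural pretest measure, but the definition puts them inside the outcome.

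**Working it through.** **Length of the lead-in.** Follow-up is 18 months, and introduction to endline is about 12 months, so 18 − 12 = about 6 months. The six-month limit on replacement is compatible with this, but it is a maximum. If the diaries last one year and also run from baseline to endline, the whole window is about 12 months and the lead-in is short. It cannot be zero, because pairing on baseline data, allocation and volunteer training all come between baseline and exposure. I therefore show 0, 3 and 6 months.

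**Reproducing the stated design.** Inputs from the Sample size section: d = 0.4, ρ = 0.014, k = 12 clusters per arm, power 80%, and 5% taken as two-sided alpha.

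- Individual randomisation: n = 2 × ((1.960 + 0.842)/0.4)² = 98.1, rounded up to 99 per arm.
- Cluster size with k fixed: m = n(1 − ρ)/(k − nρ) = 9.1 (n = 98.1) to 9.2 (n = 99), rounded up to 10. This gives 120 per arm and 240 in total, as stated.
- Design effect 1 + 9 × 0.014 = 1.126; effective n = 120/1.126 = 106.6 per arm.
- Power at 0.4 SD: 0.4 × √(106.6/2) = 2.92, and Φ(2.92 − 1.96) = 83%. With a t distribution on 22 df it is 80%.

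The sample size arithmetic is correct.

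**Dilution, if 0.4 SD is the effect over the 12 months after roll-out.** Hold that effect fixed in visits and let r = (12 + lead-in)/12. The SD of the longer count grows by √r if a household's monthly counts are independent, and by r if differences between households are fully stable. The protocol does not give the split, so these are the two extremes. The ICC is held at 0.014.

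| Lead-in | r | Effect (SD) | Power, normal | Power, t (22 df) |
|---|---|---|---|---|
| 0 months | 1.00 | 0.40 | 83% | 80% |
| 3 months | 1.25 | 0.32 to 0.36 | 65% to 74% | 61% to 70% |
| 6 months | 1.50 | 0.27 to 0.33 | 49% to 66% | 46% to 63% |

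For the 6-month row: 0.4/√1.5 = 0.327 and 0.4/1.5 = 0.267. To restore 80% power (normal approximation) with clusters of 10:

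- 2 × (2.802/0.327)² × 1.126 = 166 households per arm, or 17 clusters;
- 2 × (2.802/0.267)² × 1.126 = 249 households per arm, or 25 clusters.

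The plan has 12 clusters per arm.

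**If 0.4 SD refers to the full window.** Nominal power stays at 80-83%. With a 6-month lead-in, the effect needed over the 12 months after roll-out is 0.4 × √1.5 = 0.49 SD to 0.4 × 1.5 = 0.60 SD.

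**The case against.** The strongest reply has four parts.

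1. **The 6 months is not stated anywhere.** It is a subtraction, one of its terms is approximate, and the one-year diaries contradict it. The schedule table, which might settle the point, is not reproduced in the text at hand. This stands: the lead-in is up to about 6 months, by inference.
2. **The power loss is not established.** A reader might infer that the planned 80% power is simply lost. The documents do not support that, because the 0.4 SD has no window. The loss is conditional.
3. **The model may already exclude pre-roll-out time.** The dummy is defined by allocation alone: "It takes one if the respondent belongs to the intervention cluster and zero if control". A reader might infer that weeks before the programme existed enter the pooled model as treated outcome rows. No section says so. Equation (1) takes a posttest measure as its outcome and speaks of a post-treatment comparison, and a dummy fixed over time is normal for that. What remains is a conflict between the definition of the primary outcome and the description of the model, on a point that decides which visits count.
4. **The plan already uses baseline information.** It adjusts for a baseline measure and pairs villages on baseline outcomes, so actual power may exceed the unadjusted figures above. This stands, but adjustment does not restore the diluted effect. The protocol gives no pre/post correlation, so I attach no power gain to the proposed covariate either.

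It is also fair that, under randomisation, dilution pulls the estimate toward zero and does not inflate the false-positive rate.

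**Conclusion.** The point holds in this form. The sole primary outcome is defined over a window that opens before the intervention can act, and that definition conflicts with the post-treatment outcome described for Equation (1). It also cannot be applied to replacement households that enter after baseline. None of this depends on a power assumption.

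The size is conditional. It rests on three things that the protocol leaves open: the length of the lead-in, the window to which 0.4 SD belongs, and how the variance of the count grows with time. If 0.4 SD is the post-roll-out effect, a 6-month lead-in lowers power from about 80-83% to about 46-66%, and a 3-month lead-in lowers it to about 65-74% (normal approximation). If 0.4 SD was meant for the full window, the nominal figure survives, but the effect required of the programme rises to about 0.49-0.60 SD, which the protocol does not justify.

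**What to change.** - Define the primary count from a pre-specified roll-out date, the same calendar date for both villages of a pair, to endline.
- Use each household's pre-roll-out diary visit rate as the pretest term X_ij0 in Equation (1). A rate, unlike a count, can be used for replacement households with shorter pre-roll-out observation.
- State that pre-roll-out weeks are not outcome rows in the pooled panel.
- State which window the 0.4 SD refers to.
- Reconcile the durations in the Abstract, Expected outcomes, Baseline and endline survey instruments, and Financial and health diaries.

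**Cost.** No additional data are needed, since weekly diaries with visit dates are already planned from baseline to endline. The counting window becomes shorter. A roll-out date has to be chosen from a sequence of steps (volunteer training, wallet introduction, insurance offer), preferably before outcomes are compared by arm. The registered primary outcome needs a documented amendment, with ethical approval where the Ethical considerations section requires it.
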